## Discussion

Although treatment as prevention has already been shown to be highly effective among serodiscordant couples, further evidence is required to determine its community-level impact on HIV incidence among gay and bisexual men. This issue is particularly relevant in the Australian context, where testing and treatment coverage is high but where there has been no decline in annual HIV diagnoses [6]. The two large cohorts established in this study will provide detailed information on the level of testing and treatment coverage that can be achieved and, in the turn, the impact on HIV incidence.

While clinical trial results and modelling studies have fostered optimism about the treatment as prevention’s public health potential, the ultimate reduction of incidence may be somewhat less than expected in gay and bisexual men [26]. In Australia, an estimated 12% of people living with HIV are undiagnosed [6] with the average time between infection and diagnosis estimated to be between two and three years [22]. Undiagnosed infections contribute disproportionately to HIV transmission due to higher viral loads and sexual practices [5]. It is, therefore, a key strength of this study that it will consider the roles of diagnosed and undiagnosed HIV in onward transmission among gay and bisexual men.

There have been only a few community-level studies of treatment as prevention in gay and bisexual men [27–30]. A consistent limitation in all these studies is the indirect measurement of HIV incidence, calculated either via mathematical modelling or derived from case notifications. Although case notifications in a highly tested population may be close to reflecting incidence, in Australia nearly a quarter of diagnoses are considered ‘late’ (CD4 cell counts of <350/mm^3^) [6] and trends in notifications can be influenced by fluctuations in diagnostic testing. One large, community-level study of heterosexuals in Africa measured HIV incidence directly between 2009–2012 and demonstrated a strong correlation between treatment coverage and HIV incidence at a community-level [31]. These findings, however, cannot be applied to gay and bisexual men due to population differences in sexual behaviour and HIV incidence. In addition, the levels of HIV testing and treatment coverage reported in this study were of the levels achieved in Australia more than a decade ago. Furthermore, any community-level evaluation of treatment as prevention must account for potential confounders, including other prevention and risk reduction strategies and notably the uptake of PrEP.

Keys strengths of the TAIPAN study design are its ability to directly measure HIV incidence among gay and bisexual men, the inclusion of undiagnosed men in assessing community prevalence of viraemia, and the large patient cohorts. There are, however, some limitations to consider. First, the HIV negative cohort will include approximately half of all gay and bisexual men across both states. Although very large, the cohorts are unlikely to be fully representative of all gay and bisexual men in New South Wales and Victoria. We believe it is reasonable to assume, however, that any temporal relationships and predictors of study outcomes we detect in a cohort of this size will be applicable to the general population of gay and bisexual men. Second, during 2016 and 2017 access to PrEP has and will be expanded in both New South Wales and Victoria. This parallel prevention initiative may impact on HIV incidence but we will be able to assess and control for PrEP uptake in the multivariate analyses through prescribing data in the HIV negative cohort. Third, optimism associated with these new prevention strategies may foster changes in men’s sexual behaviour and potentially undermine the efficacy of treatment as prevention. As TAIPAN is not able to collect detailed sexual risk behaviour data, this question will be explored via separate studies.

The TAIPAN study will contribute to the growing body of literature that seeks to understand the impact of HIV treatment as prevention in a range of settings and population groups. These study outcomes will have implications for policy and practice in resource-rich countries where the epidemic mainly affects gay and bisexual men. Considering there have been significant investments in HIV testing and treatment initiatives in recent years in Australia and overseas, it is vital to assess the impact of treatment as prevention on HIV incidence.

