### Covariates

Covariates considered for this study’s analyses will include patient demographic variables (area of residence, age, indigenous status, country of birth, if Australia’s public health insurance scheme ‘Medicare’ was recorded), clinical information (HIV status, STI diagnoses, CD4 cell count and viral load results, hepatitis B and C co-infection), behavioural information (gender(s) of sexual partner, condom use, injecting drug use, recent sex work, and sexual partner numbers) and service provision - related variables (clinic location - urban vs regional/remote, service type - general practice, sexual health clinic, hospital, community-led service). Additionally, treatment information and treatment type will be used to assess the use of HIV antiretrovirals among the negative cohort as pre- and/or post-exposure prophylaxis (‘PrEP’ and ‘PEP’). The only variables likely to be missing from a substantial number of records relate to sexual risk behaviour. For this information we will draw on records from multiple sources and use a recorded diagnosis of rectal chlamydia and gonorrhoea as a surrogate marker of risk [19]. Not all covariates will be relevant to every analysis.

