### Data analyses

TAIPAN will undertake four separate analyses to address the study aims (Table 2).

TAIPAN’s primary aim will be addressed by examining the temporal relationship between community prevalence of viraemia and incidence of HIV infection in gay and bisexual men. For each year of follow up, the community prevalence of HIV viraemia as determined by the calendar year will be entered as an independent variable in the regression. In addition to estimating the effect of community prevalence of viraemia, we will control at the individual level for other demographic, clinical and behavioural determinants of acquisition of new HIV infection, and recent sexual risk practices. We will use random effects Poisson models to undertake multi-level analyses that will allow us to include group-related variables (community prevalence of viraemia), individual variables (demographic, clinical, and behavioural) and time.

The study period will be divided into three-year periods defined by treatment guidelines and policy. The first period will encompass 2009–2011 and serve as a ‘before’ treatment as prevention period. The second period will encompass 2012–2014 and represent a transition period given that several Australian jurisdictions began to expand treatment as prevention initiatives during this time. And the third period will encompass 2015–2017, representing the full implementation of treatment as prevention given that early ART initiation was recommended for both individual and public health purposes. In regards to time lags, we assume that HIV incidence is affected by the estimated prevalence of virological suppression from the preceding year.

The second analysis will examine the temporal relationship between the three time periods described above and the incidence of treatment initiation among men newly diagnosed with HIV (Secondary Aim 1). Using the study periods described above in a regression analysis, incidence of treatment initiation among men newly diagnosed with HIV will be the outcome variable while controlling for clinical, demographic and behavioural factors. Given its historical role in determining when to initiate treatment, CD4 cell count at diagnosis and HIV viral load will also be included in the multivariate model.

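### Adjusting for PrEP through records of men in the negative cohort removes users' own protection, but not all of PrEP's effect on non-users, so the viraemia coefficient may be biased in 2016–2017

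*Protocol article*

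**What the plan says.** All of this is in the Protocol article.

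- **Exposure (Data analyses).** "the community prevalence of HIV viraemia as determined by the calendar year will be entered as an independent variable in the regression". So there is one value per calendar year. On lag, "we assume that HIV incidence is affected by the estimated prevalence of virological suppression from the preceding year".
- **Other determinants (Data analyses).** "we will control at the individual level for other demographic, clinical and behavioural determinants of acquisition of new HIV infection".
- **Model terms (Data analyses).** The random effects Poisson model is to "include group-related variables (community prevalence of viraemia), individual variables (demographic, clinical, and behavioural) and time". Viraemia is the only group-level variable named, and the form of time is not given.
- **PrEP data (Covariates).** Treatment information is used "to assess the use of HIV antiretrovirals among the negative cohort as pre- and/or post-exposure prophylaxis".
- **Standard set (Discussion).** A community-level evaluation "must account for potential confounders, including other prevention and risk reduction strategies and notably the uptake of PrEP".
- **Timing (Discussion, limitations).** "during 2016 and 2017 access to PrEP has and will be expanded in both New South Wales and Victoria". Data analyses defines 2015–2017 as the period of full implementation of treatment as prevention.
- **Assurance (Discussion, limitations).** "we will be able to assess and control for PrEP uptake in the multivariate analyses through prescribing data in the HIV negative cohort".

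The article states no community-level PrEP term, no analysis ending before 2016, and no caution about PrEP's effect on men who do not take it.

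**The concern.** PrEP acts on incidence in two ways. It protects the man who takes it, and it lowers the risk of other men because fewer of their partners become infected. A PrEP indicator on each man's record handles the first. The second is shared by everyone at risk in a given year, so it varies by calendar year, as the exposure does. An individual covariate cannot remove it.

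The negative cohort is about half of the population of HIV-negative gay and bisexual men (Participants). PrEP taken by men outside it also lowers members' risk and appears in no member's record.

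Two things are at stake:

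1. The viraemia coefficient, which answers the primary aim, may carry a PrEP effect that began in the last two study years.
2. Even where PrEP's indirect effect does pass through measured viraemia, the study would read that fall in viraemia as the result of testing and treatment.

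**Working it through.** **1. What the lagged exposure can and cannot capture.** Part of PrEP's indirect effect runs through viraemia itself, because Outcome 1 counts diagnosed and undiagnosed men. That part is not confounding of the viraemia–incidence association. The one-year lag limits how much is captured:

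| Incidence year | Viraemia year used | PrEP expansion reflected in that viraemia value? |
|---|---|---|
| 2015 | 2014 | No |
| 2016 | 2015 | No, it precedes the expansion |
| 2017 | 2016 | First year only |

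The Discussion puts the average time from infection to diagnosis at two to three years. Infections averted in 2016 would therefore show mainly in the undiagnosed component, which is back-projected and not observed. A remainder outside the measured exposure is thus plausible. Call it *r*: the proportional reduction in non-users' incidence in 2017 that lagged viraemia does not carry, with half of it in 2016.

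**2. Inputs.** The plan gives no figure for this point to reproduce. Its event numbers are consistent: 0.80 × 420 = 336 per year after a 30% fall, so 420 / 0.70 = 600 and 0.80 × 600 = 480 per year before it. I use 480. If no viraemia value before 2009 is used, the lag leaves 8 incidence years, 2010–2017. *Assumed, not in the documents:* *r* of 10% or 20%, and the shape of the viraemia fall.

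**3. Hand calculation: linear viraemia fall, no time term, users' own protection already removed.** Number the years x = 1 to 8, with mean 4.5 and Σ(x − 4.5)² = 42. On the log scale the bias is the least-squares slope of the uncaptured effect, times 7 for the whole fall.

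- *r* = 10%: y₇ = ln 0.95 = −0.0513; y₈ = ln 0.90 = −0.1054. Slope = (2.5 × −0.0513 + 3.5 × −0.1054) / 42 = −0.0118. Factor = exp(7 × −0.0118) = 0.92.
- *r* = 20%: y₇ = ln 0.90 = −0.1054; y₈ = ln 0.80 = −0.2231. Slope = (2.5 × −0.1054 + 3.5 × −0.2231) / 42 = −0.0249. Factor = 0.84.
- Standard error over the whole fall with 480 events a year: 7 × √(1/(480 × 42)) = 0.049. Nominal z = 0.083/0.049 ≈ 1.7 and 0.174/0.049 ≈ 3.5, before any between-year variance.

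Poisson fits to expected counts over several curve shapes agree. These assumed PrEP coverage of 10–20% in 2017 (half in 2016) and 90% direct efficacy. The factor is 1.00 for *r* = 0, 0.91–0.94 for 10% and 0.83–0.88 for 20%. So the individual covariate removes the direct effect fully and none of *r*.

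**4. The plan's time term changes the answer (*r* = 20%).**

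- *Linear time, linear viraemia fall:* viraemia and time are collinear, so the coefficient is not estimable.
- *Linear time, curved fall:* with a quadratic curve, use the contrast (7, 1, −3, −5, −5, −3, 1, 7), whose sum of squares is 168. Coefficient = (1 × −0.1054 + 7 × −0.2231) / 168 = −0.0099; × 49 = −0.486. Factor = 0.61 if the fall is late, and 1/0.61 = 1.63 if it is early. Poisson fits gave 0.63–0.64 (late) and, with another early curve, 1.88–1.91.
- *Three policy periods:* Poisson fits gave 0.71–0.83.

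**5. The two candidate sensitivity analyses.**

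- *Ending in 2015:* the PrEP years drop out, leaving six lagged years with Σ(x − mean)² = 17.5. The standard error rises by √(42/17.5) = 1.55 for a linear fall. An S-shaped fall gave 1.5–1.6.
- *Group-level PrEP coverage, no time term:* the fits returned 1.00–1.01. That is close to guaranteed, because spillover was set to follow coverage. Coverage is zero in six of the eight years in this set-up, so the term behaves much like a 2016–2017 indicator.

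**The case against.** The strongest reply has four parts.

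- **The article does not say that PrEP enters only at the individual level.** It names a data source, and prescribing data could be aggregated by year or state. This is fair: the individual-level reading comes from taking Data analyses, Covariates and the Discussion together. But nothing stated points to aggregation, and the assurance is a positive claim, not a detail left open for a later plan.
- **Time is in the model.** True. A reader might infer that PrEP's indirect effect will be credited to falling viraemia, in favour of the study hypothesis. The documents do not support that. Depending on the form of time and the shape of the viraemia curve, the remainder could push the estimate either way or leave it not estimable. By the same token, time is not a dependable safeguard.
- **PrEP's indirect effect works through viraemia.** Largely true, and it narrows the point. A reader might treat the whole spillover as bias. Only the part missed by the lag and by the modelled undiagnosed component can bias the coefficient. For the same reason an example in which viraemia has no effect, yet fewer infectious men still protect non-users, would be strained. The factors above are therefore stated as multipliers from the uncaptured remainder alone.
- **The issue is already flagged.** PrEP is listed as a limitation, but the text then says that it can be controlled. That second statement is what goes too far.

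**Conclusion.** The point holds as a risk of bias, not as a demonstrated bias. Adjustment through the records of men in the negative cohort can deliver control of PrEP's direct effect. It cannot deliver control of the effect on non-users, including that from PrEP used outside the cohort, beyond what lagged viraemia captures. PrEP's expansion falls in two of the three full-implementation years, so calendar time does not separate the two influences well.

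With no time term, a remainder of 10% in 2017 multiplies the estimated rate ratio by roughly 0.91–0.94, and 20% by 0.83–0.88. The 10% case has a nominal z of about 1.7 and would not reach p < 0.05 alone. With a time term the direction is open. These sizes rest on assumed coverage, spillover and curve shapes, none of which the document gives.

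Separately, any PrEP-driven fall in viraemia would be attributed to treatment. Under the one-year lag this concerns mainly the pairing of 2017 incidence with 2016 viraemia. No sample-size figure is affected.

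**What to change.** 1. Pre-specify a sensitivity analysis of the primary association restricted to incidence up to 31 December 2015, with the same form of time as the main model, and report it beside the 2009–2017 estimate.
2. As a further sensitivity analysis, add annual PrEP coverage from the prescribing data, by state if possible, as a group-level covariate next to viraemia. Say that over about eight lagged annual values it is only weakly separable from viraemia and time.
3. Reword the limitation in the Discussion: individual adjustment controls direct PrEP effects only, and a fall in viraemia in the PrEP years cannot be credited to treatment alone.

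**Cost.** One additional restricted fit, one derived variable from data already to be collected, and one more model. The fit to 2015 is less precise (standard error about 1.5 times larger under the assumed inputs). It also leaves out two of the three full-implementation years and, with the lag, uses no viraemia value after 2014. It should therefore be a companion to the main estimate and not a condition on the study's conclusion.

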## Abbreviations

ACCESS: Australian Collaboration for Coordinated Enhance Sentinel Surveillance of Sexually Transmissible Infections and Blood Borne Viruses
AIDS: Acquired immune deficiency syndrome
ART: Antiretroviral therapy
HIV: Human immunodeficiency virus
PEP: Post-exposure prophylaxis
PrEP: Pre-exposure prophylaxis
TAIPAN: Treatment with antiretrovirals and their impact on positive and negative men
